#### 4.6 Radiation Adverse Events

The consequences of laryngeal toxicity and cough will be monitored and graded according to the Common Terminology Criteria for Adverse Effects (CTCAE) v4.

#### 4.7 Serious Adverse Event Reporting

##### Adverse Events: Definitions and Reporting

Adverse Events will be reported as indicated by the appropriate following table (see below).

##### Definition

An adverse event is defined as any untoward or unfavorable medical occurrence in a human research study participant, including any abnormal sign (for example, abnormal physical exam or laboratory finding), symptom, clinical event, or disease, temporarily associated with the subject's participation in the research, whether or not it is considered related to the subject's participation in the research.

Adverse events encompass clinical, physical and psychological harms. Adverse events occur most commonly in the context of biomedical research, although on occasion, they can occur in the context of social and behavioral research. Adverse events may be expected or unexpected.

##### Severity

Adverse events will be graded by a numerical score according to the defined NCI Common Terminology Criteria for Adverse Events (NCI CTCAE) and version number specified in the protocol. Adverse events not specifically defined in the NCI CTCAE will be scored on the Adverse Event log according to the general guidelines provided by the NCI CTCAE and as outlined below.

- Grade 1: Mild
- Grade 2: Moderate
- Grade 3: Severe or medically significant but not immediately life threatening

- Grade 4: Life threatening consequences
- Grade 5: Death related to the adverse event

### Serious Adverse Events

ICH Guideline E2A and the UTSW IRB define serious adverse events as those events, occurring at any dose, which meets any of the following criteria:

- Results in death
- Immediately life-threatening
- Results in inpatient hospitalization or prolongation of existing hospitalization
- Results in persistent or significant disability/incapacity
- Results in a congenital anomaly/birth defect
- Based upon appropriate medical judgment, may jeopardize the subject's health and may require medical or surgical intervention to prevent one of the other outcomes listed in this definition.

Note: A "Serious adverse event" is by definition an event that meets any of the above criteria. Serious adverse events may or may not be related to the research project. A serious adverse event determination does not require the event to be related to the research. That is, both events completely unrelated to the condition under study and events that are expected in the context of the condition under study may be serious adverse events, independent of relatedness to the study itself. As examples, a car accident requiring overnight hospitalization would be a serious adverse event for any research participant; likewise, in a study investigating end-stage cancer care, any hospitalization or death would be a serious adverse event, even if the event observed is a primary clinical endpoint of the study. Refer to the UTSW IRB website at <http://www.utsouthwestern.net/intranet/research/research-administration/irb/study-management/adverse-events.html> to determine when a serious adverse event requires reporting to the IRB.

### Unanticipated Problems:

The term "unanticipated problem" is found, but not defined in the regulations for the Protection of Human Subjects at 45 CFR 46, and the FDA regulations at 21 CFR 56. Guidance from the regulatory agencies considers unanticipated problems to include any incident, experience, or outcome that meets each of the following criteria:

- Unexpected (in terms of nature, severity or frequency) AND
- Definitely, probably, or possibly related to participation in the research AND
- Serious or a possible unexpected problem in that the research places subjects or others at greater risk of harm than was previously known or recognized. Note: Any serious adverse event would always suggest a greater risk of harm.

### Follow-up

All adverse events will be followed up according to good medical practices.

### Reporting

Local unanticipated problems require expedited reporting, and are submitted to the UTSW IRB through the UTSW eIRB and to the SCC DSMC Coordinator. Hardcopies or electronic versions of the eIRB report; FDA Form #3500A forms, or other sponsor forms, if applicable; and/or any other supporting documentation available should be forwarded to the DSMC Coordinator. The DSMC Coordinator forwards the information onto the DSMC Chairman who determines if immediate action is required. Follow-up eIRB reports, and all subsequent SAE documentation

that is available are also submitted to the DSMC Chair who determines if further action is required.

All local serious adverse events which occur on research subjects on protocols for which the SCC is the DSMC of record require reporting to the DSMC regardless of whether IRB reporting is required. Hardcopies or electronic versions of the FDA Form #3500A forms, or other sponsor forms, if applicable; and/or any other supporting documentation available should be forwarded to the DSMC Coordinator.

If the event occurs on a multi-institutional clinical trial coordinated by the Cancer Center, the DOT Manager or lead coordinator ensures that all participating sites are notified of the event and resulting action, according to FDA guidance for expedited reporting. DSMC Chairperson reviews all serious adverse events within upon receipt from the DSMC Coordinator. The DSMC Chairperson determines whether action is required and either takes action immediately, convenes a special DSMC session (physical or electronic), or defers the action until a regularly scheduled DSMC meeting.

Participating sites of multi-institutional clinical trials coordinated by the UTSW Radiation Oncology:

Written reports to

UTSW Radiation Oncology Study Coordinator or Clinical Research Manager within 1 working day  
Email: [[contact]](mailto:[contact]) or [[contact]](mailto:[contact])

[contact]

UTSW Radiation Oncology Study Coordinator or Clinical Research Manager will report to UTSW SCC Data Safety Monitoring Committee Coordinator

UTSW SCC Data Safety Monitoring Committee Coordinator  
Email: [[contact]](mailto:[contact])  
[contact] or deliver to [name]

UTSW Institutional Review Board (IRB)

Submit via eIRB with a copy of the final sponsor report as attached supporting documentation

1. SAEs  
Local serious adverse events (SAEs) for studies where SCC DSMC is the DSMC of record require reporting to the DSMC coordinator within 2 working days of PI awareness, or as described in the protocol.
2. Unanticipated Problems
  - Local unanticipated problems require reporting to the UTSW IRB within 2 working days of PI awareness of the event.
  - Unanticipated problems, including those that occur as non-local events, require reporting to the UTSW IRB within 10 working days of PI awareness of the event.

For further guidance for Investigators regarding safety reporting requirements for INDs and BA/BE studies, refer to FDA Draft Guidance document:

<http://www.fda.gov/downloads/Drugs/GuidanceComplianceRegulatoryInformation/Guidances/UCM227351.pdf>

Attribution of an event can be categorized as: unrelated, unlikely, possible, probable, or definitely related.

Adverse events (below grade 3) do not need to be submitted immediately. Rather, they should be documented in the Adverse Events CRF along with a brief description of the event, grade, and attribution).

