| Grade 5 Death                                                                                                                          | Termination of trial with reporting of dose limiting toxicity |
| Hypoparathyroidism                                                                                                              |                                                               |
| Grade 1 Asymptomatic; clinical or diagnostic observations only; intervention not indicated                                             | None                                                          |
| Grade 2 Moderate symptoms; medical intervention indicated                                                                              | None                                                          |
| Grade 3 Severe symptoms; medical intervention or hospitalization indicated                                                             | See Section 10 Statistical Considerations                     |
| Grade 4 Life-threatening consequences; urgent intervention indicated                                                                   | Termination of trial with reporting of dose limiting toxicity |
| Grade 5 Death                                                                                                                          | Termination of trial with reporting of dose limiting toxicity |

Dose limiting toxicities (DLT) will be defined as occurring whenever any one of the following are manifested as occurring whenever any one of the following are manifested: laryngeal edema (grade 4 or 5), dyspnea (grade 4 or 5), stridor (grade 4 or 5) probably or definitely related to the protocol.

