##### **5.1.8 Adverse event assessment**

All acute and late adverse events from protocol radiation therapy will be reported and scored for severity using the NCI Common Terminology Criteria for Adverse Events (CTCAE) version 4.0. A copy of the CTCAE v4.0 can be downloaded from the CTEP home page (<http://ctep.info.nih.gov>).

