## **10.0 Statistical Considerations**

### **10.1 Primary endpoint**

The primary endpoint of this phase I clinical trial will be to either reach the minimum number of fractions that is tolerated for larynx irradiation or a dose of 42.5 Gy in 5 fractions whichever comes first. Patients will be treated in cohorts of 3-15. Toxicity will be graded using the National Cancer Institute (NCI) Common Toxicity Criteria for Adverse Events (CTCAE) version 4.0. A dose-limiting toxicity (DLT) is a grade 3 or greater toxicity definitely related to treatment in the following categories: laryngeal edema, voice, dyspnea, stridor, or cough. All reported DLTs will be verified by the study

chair, data monitoring committee, and as appropriate, independent review before final determination that a DLT has in fact occurred. The number of fractions will be reduced from 15, to 10 fractions, and then to 5 fractions (reduced by 5 fractions per step). The phase 1 portion of the study will be completed with either of the following events occur: 1) the MTD for a cohort is reached or 2) when the lowest number of fractions is treated and tolerated (42.5 Gy in 5 fractions).

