## 10.2 Phase 1 waiting periods

Fraction reduction for this phase 1 clinical trial will not occur until sufficient waiting has occurred after a cohort has been treated. A period of 90 days must pass before further fraction reduction for the purpose of assessing toxicity. If 90 days have passed without a DLT at a dose level, the trial will be allowed to the next level, so long as either criteria for defining the MTD or criteria for further fraction reduction is not reached. If the maximum number of patients are enrolled to a given fraction level, yet criteria for follow-up is not reached in a representative sample of patients, further enrollment to the protocol will be suspended until adequate follow-up is reached. No action will be taken for Grade 1 or Grade 2 toxicities. If any 2 Grade 3 toxicities occur within a dose level likely or definitely related to radiation therapy, the trial will be terminated with reporting of DLT at that dose level. Any Grade 4 or Grade 5 toxicity found to be likely or definitely related to treatment will result in termination of the trial with reporting of DLT at that dose level.

Grade 3 toxicities likely or definitely related to protocol therapy will result in action in schema provided below:

[figure not shown]

For level -1, if a Grade 3 toxicity occurs, the trial will be terminated with reporting of DLT.

For level 0, if a Grade 3 toxicity occurs, a step de-escalation will occur to level -1. If no grade 3 toxicities are experienced at level 0, the trial will proceed to level 1.

---

For level 1, if there are no Grade 3 toxicities after initial enrollment of 7 patients, an additional 8 patients will be enrolled. If there is no grade 3 toxicity after enrollment of an additional 8 patients, the trial will proceed to level 2. If there is a 1 grade 3 toxicity in the additional 8 patients, the trial will proceed to level 2 at the discretion of the PI and DSMC.

For level 1, if there is 1 Grade 3 in the initial 7 patient cohort, an additional 8 patients will be enrolled. If there is an additional Grade 3 toxicity at this level, the trial will be terminated with reporting of DLT. If there are no further grade 3 toxicities in the additional 8 patients, proceeding to the next level will be done at discretion of the DSMC and PI.

For level 1, if there are 2 grade 3 toxicities in the initial 7 patient cohort, the trial will be terminated with reporting of DLT.

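### Three different attribution thresholds govern the toxicity counts, and verification covers only reported DLTs, so no written step can add a grade 3 or higher event first given a lower attribution

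*Protocol*

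**What the plan says.** The Reporting part of protocol Section 4.7 gives the scale: "Attribution of an event can be categorized as: unrelated, unlikely, possible, probable, or definitely related". It does not say who assigns the category.

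Three places then decide which toxicities matter for the levels:

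- **Section 4.1**, the DLT definition after the toxicity tables, covers grade 4 or 5 laryngeal edema, dyspnea and stridor. It ends: "stridor (grade 4 or 5) probably or definitely related to the protocol".
- **Section 10.1**: "A dose-limiting toxicity (DLT) is a grade 3 or greater toxicity definitely related to treatment in the following categories". The categories are laryngeal edema, voice, dyspnea, stridor and cough.
- **Section 10.2**: "Grade 3 toxicities likely or definitely related to protocol therapy will result in action in schema provided below". The same *likely or definitely* wording governs the two-event termination rule and the termination rule for grade 4 or 5 events.

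On checking, Section 10.1 says: "All reported DLTs will be verified by the study" chair and the data monitoring committee, with independent review where appropriate, before it is finally determined that a DLT occurred.

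**The concern.** The level decisions rest on very small counts. At level 0 one grade 3 toxicity triggers a step back, and at levels 1 and 2 a second one ends the trial. Which events enter the count therefore matters a great deal, and the protocol leaves this open in two ways.

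First, the threshold depends on which section is read. An event rated *probable* is outside the 10.1 definition and inside the 4.1 wording on attribution. In 10.2 it is inside only if *likely* is taken to mean *probable*. An event rated *possible* is outside all three.

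Second, the only verification step tied to DLT status starts from events already reported as DLTs. It can correct an event that was wrongly reported. It does not provide for an event that was initially under-attributed.

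Ambiguous attribution is plausible here. Section 1.3 expects dose-limiting toxicity to appear as hoarseness, stridor or cough, in patients whose tumor is on the vocal cord. Section 3.2 excludes only those who smoke more than 2 packs a day. If treatment-related events are rated below the threshold, the trial moves more easily to fewer, larger fractions.

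**Working it through.** **The thresholds side by side, on the 4.7 scale**

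| Rating | 4.1 | 10.1 | 10.2 |
|---|---|---|---|
| definite | meets | meets | meets |
| probable | meets | does not | unclear (*likely* is not on the scale) |
| possible | does not | does not | does not |
| unlikely, unrelated | does not | does not | does not |

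The table compares attribution only. Sections 4.1 and 10.1 also differ in grade and in categories.

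**Inputs for the size of the effect**

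- Level 1 enrolls 7 + 8 = 15 patients (Section 10.2). The cohort sizes in the schema table reproduce the stated totals: 3 + 7 + 7 = 17 and 3 + 15 + 15 + 15 = 48.
- Level 1 terminates at 2 counted grade 3 toxicities. With 0 it proceeds to level 2. With exactly 1, proceeding is at the discretion of the PI and DSMC (Section 10.2).
- The true rate *p* of treatment-related grade 3 toxicity is not in the protocol. It is assumed at 10%, 20% and 30%.
- The share *s* of those events rated below the counting threshold is not in the protocol. It is assumed at 0, one quarter and one half.

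**Formulas**

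The counted rate is *p*′ = *p*(1 − *s*). With 15 patients:

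- P(0 counted) = (1 − *p*′)^15
- P(1 counted) = 15 *p*′ (1 − *p*′)^14
- P(not terminated) = P(0) + P(1)

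The split into 7 and 8 does not change the last figure, because the level stops only when the second event is reached.

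**Numbers at *p* = 20%**

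- *s* = 0, *p*′ = 0.20: 0.0352 + 0.1319 = 0.167
- *s* = 1/4, *p*′ = 0.15: 0.0874 + 0.2312 = 0.319
- *s* = 1/2, *p*′ = 0.10: 0.2059 + 0.3432 = 0.549

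**Range over the assumed rates**

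| True rate | Not terminated: none / quarter / half missed | 0 counted: none / quarter / half missed |
|---|---|---|
| 10% | 54.9% / 68.8% / 82.9% | 20.6% / 31.1% / 46.3% |
| 20% | 16.7% / 31.9% / 54.9% | 3.5% / 8.7% / 20.6% |
| 30% | 3.5% / 11.7% / 31.9% | 0.5% / 2.2% / 8.7% |

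At level 0 with 3 patients and *p* = 20%, the chance of no counted event is 0.8³ = 51.2% if all count and 0.9³ = 72.9% if half are missed.

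The calculation treats every event as grade 3. It ignores the rule that a single likely or definitely related grade 4 or 5 event ends the trial.

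**The case against.** A reader might infer that *possible* events never count, that the committee can never add one, and that the DLT count is therefore biased downward. The documents do not support this, for these reasons:

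- **The DSMC sees more than reported DLTs.** All local SAEs go to it whatever their relatedness (4.7). Section 6.0 has it review SAEs in real time and adverse events quarterly. Its Chairperson may act at once or convene a special session. Grade 3 laryngeal edema is defined by an indication for hospitalization, so it would ordinarily reach the DSMC as an SAE. Nothing bars the DSMC from disputing an attribution, and 6.0 refers to an operations manual for the detailed monitoring plan.
- **One DLT route needs no attribution category.** Section 4.13 counts 3 or more treatments missed due to toxicity as a DLT.
- **The attributor is not named**, so a filter applied by the investigator alone is an inference.
- **The direction is conditional.** Leaving out *possible* events lowers the count only if some are truly treatment-related. Removing a wrongly reported DLT corrects an error in the other direction.
- **Not terminated is not the same as advancing.** Of the 54.9%, 34.3 points are the one-event case, which Section 10.2 sends to the PI and DSMC.

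Two further inferences also fail. Section 5.1.8 says "All acute and late adverse events from protocol radiation therapy will be reported and scored for severity", which might be read as leaving out unrelated events. But 4.7 defines adverse events regardless of relation, grades them all and records attribution. For unanticipated problems, 4.7 accepts "Definitely, probably, or possibly related to participation in the research". That is an IRB reporting threshold with a different purpose, and a difference from the level rules is not a contradiction.

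These points remove the absolutes and leave a narrower gap. A general power to act is not an adjudication rule, and nothing in the protocol links DSMC review to the 10.2 counts. Grade 3 voice change and cough are defined without hospitalization and need not be SAEs. The missed-treatment route cannot catch toxicity that appears after treatment, which the 90-day wait is there to observe.

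**Conclusion.** The point holds as a defect of definition and procedure. The three thresholds disagree, and one uses a word that is not on the protocol's scale. The verification step in 10.1 can confirm or remove a counted event but has no written counterpart for adding one.

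This is not a demonstrated downward bias. It becomes one only if some treatment-related grade 3 or higher events are rated below the threshold, and the protocol gives no figure for that share or for the true toxicity rate. Under the assumed 20% rate the effect is large enough to matter. If half are missed, the chance of escaping termination at level 1 goes from 16.7% to 54.9%, and the chance of automatic progression from 3.5% to 20.6%. The change should be made because the counts are small and the conflicting passages need reconciling in any case.

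**What to change.** 1. Reconcile Sections 4.1, 10.1 and 10.2 to a single attribution threshold in the terms of the 4.7 scale, and replace *likely* with a category on that scale. The sponsor should decide whether *possible* counts. This review does not propose a threshold.
2. In 10.1, send every grade 3 or higher event in the listed categories to the existing verification step, whatever its initial attribution.
3. In 10.2, state that the level counts use the verified attribution.

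Section 5.1.8 needs no change on this account. The cost is an amendment to the wording of three sections and a few more case reviews, in a trial of at most 48 patients, by a committee that already receives these events.

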#### **4.8 Concomitant Medications/Treatments**

Concomitant use of immunosuppressant agents such as inhibitors of the mammalian target of rapamycin (mTOR), chronic high-dose steroids, small-molecule immune modulating agents will be prohibited. Anti-coagulant medications such as Coumadin, Heparin, Lovanox, Agatroban or other agents affecting the coagulation cascade will be prohibited.

#### **4.9 Other Procedures**

For dose level 1 and 2, a dexamethasone 4 mg oral tablet will be administered one hour prior to initiation of radiation therapy.

#### **4.10 Duration of Therapy**

The end of protocol therapy will occur if:

- Inter-current illness that prevents further administration of treatment
- Unacceptable adverse event(s)
- Subject decides to withdraw from the study, or
- General or specific changes in the patient's condition render the subject ineligible for further treatment at the discretion of the investigator or treating physician

#### **4.11 Duration of Follow-Up**

Subjects will be followed for 5 years after completion of radiation therapy or until death, whichever occurs first. Subjects removed from treatment for unacceptable adverse events will be followed until resolution or stabilization of the adverse event. First follow-up after completion of treatment will occur at four weeks. Thereafter, protocol required follow-up in the Radiation Oncology Clinic or Otolaryngology Clinic will occur at every 3 months for the first year, every 6 months for the second year, and annually for years 3, 4, and 5 following treatment.

#### **4.12 Removal of Subjects from Protocol Therapy**

Subjects will be removed from therapy if dose limiting toxicity is experienced. The Principal Investigator will be notified, and reason documented for study removal and the date the subject was removed in the Case Report Form. The subject should be followed-up per protocol.

#### **4.13 Subject Replacement**

Three subjects within dose levels -1 and 0 must be observed for 90 days before accrual to the next higher dose level may begin. For level 1, 7 patients must be observed for 90 days before accrual to the next higher dose level. If a subject is withdrawn from the study prior to completing therapy without experiencing a dose limiting toxicity prior to withdrawal, an additional subject may be added to that dose level. Subjects missing 3 or more radiation treatments due to toxicity will not be replaced since these subjects will be considered to have experienced a dose limiting toxicity.

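### Section 4.13 ties the level-1 90-day wait to 7 patients, but every Section 10.2 route to level 2 is decided on 15, so level 2 could open with up to 8 of 15 not yet at 90 days

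*Protocol*

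**What the plan says.** Section 4.13 (Subject Replacement) gives the only patient count attached to the level-1 wait: "For level 1, 7 patients must be observed for 90 days before accrual to the next higher dose level".

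Section 10.2 gives three routes from level 1 to level 2:

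- No grade 3 event in the first 7 and none in the next 8. This route is automatic: "If there is no grade 3 toxicity after enrollment of an additional 8 patients, the trial will proceed to level 2".
- None in the first 7 and one in the next 8. This route is left to the PI and DSMC: "If there is a 1 grade 3 toxicity in the additional 8 patients, the trial will proceed to level 2 at the discretion".
- One in the first 7 and none in the next 8. The level is first expanded: "For level 1, if there is 1 Grade 3 in the initial 7 patient cohort, an additional 8 patients will be enrolled". The PI and DSMC then decide: "If there are no further grade 3 toxicities in the additional 8 patients, proceeding to the next level will be done at discretion".

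Section 10.2 also sets a general wait once a cohort has been treated: "A period of 90 days must pass before further fraction reduction for the purpose of assessing toxicity". If a level is full, it suspends enrolment while follow-up is short, but the trigger is worded "yet criteria for follow-up is not reached in a representative sample of patients", with no number. Section 10.1 says "Patients will be treated in cohorts of 3-15", whereas 10.2 applies the word cohort to the initial 7 patients at a level.

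The Study Schema gives a total of 17 to 48 patients. Section 1.3 says that the waiting periods are there so that fractions are not reduced before toxicity has been observed.

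**The concern.** The step from level 1 to level 2 is the largest rise in dose per fraction in the trial: 4.5 to 8.5 Gy, against 3.33 to 4.5 Gy at the step before. It is where the wait matters most. The decision rule uses 15 patients, while the only numbered follow-up requirement covers 7.

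If a site treats the 7 in 4.13 as sufficient, some of the last 8 may have had only their day-1 and weekly toxicity checks, and the 4-week visit if due, when level 2 opens. A related grade 3 event in one of them before day 90 could then be the second at level 1, which 10.2 says ends the trial. By then, patients may already have received 8.5 Gy fractions.

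The stated minimum of 17 shows the same mismatch, since it counts 7 patients at level 1.

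**Working it through.** **Patient counts.** The per-level minima in Section 4.1 are 3 (level 0), 7 (level 1) and 7 (level 2). Their sum, 3 + 7 + 7 = 17, reproduces the stated minimum. The Schema maxima give 3 + 15 + 15 + 15 = 48, which reproduces the stated maximum.

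Under 10.2, every route to level 2 uses 7 + 8 = 15 level-1 patients, and level 2 also goes on to 15 unless it is stopped. Completing level 2 therefore needs at least 3 + 15 + 15 = 33. A trial stopped early can enrol fewer: at most 3 + 7 = 10 if it stops within the first 7 at level 1 without using level -1 and with 3 patients at level 0. So 17 is neither the fewest that could be enrolled nor the fewest that could complete the plan.

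**Patients possibly short of 90 days.** If 4.13 sets the number, 15 - 7 = 8.

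Whether all 8 are short depends on accrual. Ten fractions at 3 per week end on about day 22. Ninety days after that is day 22 + 90 = 112, or 16 weeks from a patient's first fraction. Assume that the last 8 start at even spacing of s days and that level 2 opens when the last one starts. A patient who started k places before the last is short if k × s < 112.

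- s = 14: 7 × 14 = 98 < 112, so all 8 are short.
- s = 30: 3 × 30 = 90 < 112 but 4 × 30 = 120, so 4 are short.
- s = 60: 1 × 60 = 60 < 112 but 2 × 60 = 120, so 2 are short.

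The protocol gives no accrual rate, so these spacings are assumptions.

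**Illustration of size.** The protocol gives no grade 3 rate and no onset times, so both are assumed. Let p be the 90-day rate of related grade 3 events, with patients independent. The first 7 are fully observed, X ~ Bin(7, p). The last 8 are partly observed, Y ~ Bin(8, p × f), where f is the share of their 90-day events already seen.

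- Automatic opening: P(X=0) × P(Y=0).
- Discretionary opening possible: P(X=0) × P(Y=1) + P(X=1) × P(Y=0).

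At p = 0.20 and f = 0.5:

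- Automatic: 0.8^7 × 0.9^8 = 0.210 × 0.430 = 0.090.
- Discretionary: 0.210 × 0.383 + 0.367 × 0.430 = 0.238.
- Total: 0.329.

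Each cell shows automatic + discretionary = chance of at most one event seen:

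| p | f = 1 (all 15 observed) | f = 0.5 | f = 0 (bound) |
|---|---|---|---|
| 0.05 | 0.463 + 0.366 = 0.829 | 0.570 + 0.327 = 0.897 | 0.698 + 0.257 = 0.956 |
| 0.10 | 0.206 + 0.343 = 0.549 | 0.317 + 0.380 = 0.698 | 0.478 + 0.372 = 0.850 |
| 0.20 | 0.035 + 0.132 = 0.167 | 0.090 + 0.238 = 0.329 | 0.210 + 0.367 = 0.577 |
| 0.30 | 0.005 + 0.031 = 0.035 | 0.022 + 0.099 = 0.121 | 0.082 + 0.247 = 0.329 |

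(Sums are of unrounded terms.)

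After an automatic opening, each of the last 8 has a remaining risk r = p(1 - f)/(1 - p × f). At p = 0.20 and f = 0.5, r = 0.10/0.90 = 0.111, and the chance of at least one later grade 3 event is 1 - (1 - 0.111)^8 = 0.61. The same formula gives 0.35 at p = 0.10 and 0.79 at p = 0.30.

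**The case against.** The strongest reply is that the protocol already intends a level-wide wait. The Study Schema treats the patients in a dose cohort as one group for fraction reduction and describes successive cohorts as successive fraction steps. Section 10.1 speaks of the MTD for a cohort in the same sense. Section 10.2 lets the trial move on when 90 days have passed without a DLT at a dose level, and its 7 are always the initial cohort. On this reading, 4.13 is a floor that matches the minimum-patients column in 4.1, and the two sections can both be met. This stands as the more natural intent, so a reader who infers a flat contradiction, or a protocol that plainly permits level 2 on 7 patients' follow-up, goes further than the text.

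It does not close the gap. The suspension clause applies in exactly this situation, with level 1 full at 15, yet it asks only for a representative sample. No sentence says how many of the last 8 must reach 90 days.

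Other replies also carry weight:

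- The enrolment wording in the automatic route proves little, because 10.2 uses similar wording for the first 7, whom 4.13 does require to be observed.
- The f = 0 column is a bound, not a forecast, given the weekly checks and the 4-week visit.
- The table totals include discretionary routes. A reader might take 58% as the chance that level 2 opens, but it is a bound on the chance that the rules would allow it.
- At low event rates the effect is small: at 5%, 83% against at most 96%.
- Late level-1 events still count towards the two-event stop, and the DSMC reviews serious events as they are reported.

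**Conclusion.** The point holds as an ambiguity in a safety rule. The text leans towards a wait for the whole level, but the only count is 7 and the suspension clause has no number. A site following 4.13 could open the 8.5 Gy step with up to 8 of 15 level-1 patients (53%) short of 90 days. That figure is an upper bound: under the assumptions above, all 8 are short at one patient every two weeks, and about 4 at one a month.

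The probabilities are illustrations under assumed rates and onset times, and no toxicity rate in the protocol supports any one row. The 10.2 diagram is not shown and may resolve the question, which keeps confidence at medium.

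The minimum of 17 is the sum of the per-level minima and fits no 10.2 path through a completed level 2, which needs at least 33. A reader might infer a minimum of 3 + 15 + 7 = 25 for a trial that stops on the initial 7 at level 2. That does not follow, because one related grade 4 or 5 event, or two grade 3 events, can end the trial at 3 + 15 + 1 = 19 or 3 + 15 + 2 = 20 patients.

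The wording is worth correcting because it protects patients at the largest dose-per-fraction step at little cost.

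**What to change.** 1. In 4.13 and 10.2, require all evaluable level-1 patients (15) to complete 90-day observation before level 2 accrual begins, on all three routes.
2. In the automatic route ("If there is no grade 3 toxicity after enrollment of an additional 8 patients, the trial will proceed to level 2"), make the condition completed 90-day observation of the additional 8 patients instead of their enrolment.
3. In the suspension clause ("yet criteria for follow-up is not reached in a representative sample of patients"), replace the representative sample with all evaluable patients at that level.
4. Restate the minimum of 17: completing level 2 needs at least 33 (3 + 15 + 15), and a trial stopped early for toxicity may enrol fewer. Do not give 25 as a minimum.

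The cost is amendment wording and an accrual pause of up to about 3 months after the last level-1 patient finishes treatment, or about 16 weeks from that patient's first fraction. Section 10.2 appears to intend this pause already.
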